### **1. Project Title**

**“LeAf Trauma - Quality of Life and Work Ability after Trauma” - Quantitative Study Components**

### **2. Project Summary**

#### **2.1 Scientific Description**

The outcome of severely injured patients depends on multiple factors. The treatment pathway is characterized by transitions between sectors (e.g., emergency services > hospital > rehabilitation > outpatient follow-up) and interdisciplinary treatment that supports various aspects of recovery. The project "LeAf Trauma" aims to identify modifiable risk factors and quantify their influence to derive measures and recommendations for improving patient care and reducing barriers in the patient pathway. The patient-relevant endpoints are health-related quality of life (hrQoL) and the restoration of work ability (AF), which serve as indicators of the multidimensional recovery of severely injured patients (functionality, psychological and physical resilience). The perspectives and needs of the affected individuals will be incorporated through patient-reported experience measures (PREM), which will be developed in the project with the expertise of experts and former trauma patients, as well as collective and project-specific patient-reported outcome measures (PROM). Through patient and expert interviews, target-oriented data collection processes will be developed, which, when implemented in the study hospitals, should ensure high acceptance and response rates in the follow-up of severely injured patients.

This mixed-method study does not involve any intervention. The individual data sources (statutory health insurance data, registry data, qualitative and quantitative data from surveys) will not be linked. Furthermore, only the results and findings derived from the analyses will be compiled to identify recommendations for care.

## 2.2 Type of Study

- Medical, non-interventional research in conjunction with medical care
- Retrospective anonymized data analysis

## 2.3 Overview of Study Design and Methodology

**2.3.1 Qualitative Prospective Study Arm** Intersectoral and interprofessional examination of the treatment process through semi-structured interviews with healthcare providers involved in the care of severely injured patients.

**2.3.2 Quantitative Prospective Cohort Study** Population-based, prospective, multicenter cohort study involving severely injured patients, with baseline data collected at discharge and follow-up surveys at 6, 12, and 18 months post-trauma.

**2.3.3 Retrospective Study Arm** Aggregated results from routine data of the Scientific Institute of the AOK (WIdO) to characterize the temporal and content-related post-hospital treatment pathways of severely injured patients until the restoration of work ability over three years. Additionally, supplementary anonymized data from the "Trauma Register of the German Society for Trauma Surgery (DGU)" (for example, regarding injuries, representativeness) will be included.

## 3. Responsibilities

### 3.1 Responsible Study Leaders and Involved Scientists

The following table (Tab. 1) lists all consortium partners involved in the study, as well as the physicians and scientific staff involved:

### **3.2 Funding**

Innovation Committee at the Joint Federal Committee

### **3.3 Registration in the Study Register**

German Clinical Trials Register (DRKS): DRKS00028841

## **4. Scientific Background**

In Germany, approximately 30,000 people suffer a severe trauma each year (annual reports of the “Trauma Register DGU”). In recent decades, significant progress in preclinical and clinical treatment has markedly reduced the mortality rate of severely injured patients (Ruchholtz et al., 2008). With increasing survival rates, the functional outcomes and health-related quality of life of these patients are becoming more important. Affected patients suffer from chronic pain, psychosomatic disorders, and unemployment (Simmel et al., 2010; Simmel et al., 2013), as well as increased post-traumatic morbidity (Bouillon et al., 1998; Holtslag et al., 2007; von Rüden et al., 2013).

The return of patients to the workforce is important to promote their quality of life and social participation and to reduce the socioeconomic burden on society due to disability. According to current data from the “Trauma Register DGU,” 60% of severely injured patients in Germany are of working age (18-65 years), and three-quarters are male. With a current legal retirement age of 67 years, disability can lead to a financial gap of several decades. The high unemployment rate after trauma is well-known. According to the Hannover Polytrauma Long-Term Study (HLPS) (Sittaro et al., 2007), an average of about 22% of patients who were previously able to work are unemployed. Another 16% have undergone retraining due to their

accident to maintain work ability, and 24% have been classified for early retirement due to the accident. According to a Dutch study, only 58.5% of the severely injured patients of working age who were followed up were able to engage in full-time employment 15 months after the trauma, and an additional 21.5% could only pursue part-time employment (Holtslag et al., 2007). According to data from a pilot study on outcome assessment, only about 30% of all severely injured patients in Germany are able to work again two years after an accident (Kamp et al., 2019).

Following predictors of clinical treatment for disability have already been identified: patient age, severity of injury, traumatic brain injury, duration of intensive medical treatment, psychological sequelae, subjective perception of the injury, and the patient's education level (Frink et al., 2014; Kaske et al., 2014).

However, the question of why patients are not able to return to work or are able to work but unemployed has not yet been investigated. Causes could be of an organizational nature, such as delays in rehabilitation or funding for retraining. Following acute medical care in a trauma center, rehabilitation measures often follow.

The success of this therapy is determined not by its duration but by the quality of the rehabilitation (Simmel et al., 2009). Organizational constraints often lead to delays in the rehabilitation measures, creating what is known as the rehabilitation gap. Currently, there is no validated instrument for assessing the quality of rehabilitation. Therefore, it is not possible to evaluate which measures and aids are typically needed after a severe trauma. There is also little evidence regarding the duration of the rehabilitation measures. However, the timing of when the rehabilitation measure begins seems to have an impact.

Another issue is that there is a lack of patient-specific feedback on long-term outcomes after the discharge of severely injured patients from acute inpatient care. Without such feedback, quality assurance in the acute clinic ends with the patient's discharge, and opportunities to improve patient care are limited to assessing the achieved discharge status. However, particularly for severely injured patients, a lengthy recovery phase is to be expected, in which acute inpatient treatment is just the beginning of a long treatment chain. Previous outcome studies have addressed specific questions (Janssen et al., 2008; Tecic et al., 2013). However, the depiction of the care reality throughout the entire recovery period and across sector boundaries, as well as the inclusion of patient experiences and needs along this path, is still pending.

## **5. Project Objectives**

The short-term project goal is to identify relevant and modifiable determinants for health-related quality of life and work ability in the care of severely injured patients, incorporating patient-reported experiences (PREs) and patient-reported outcomes (PROs). The long-term goal is to optimize the quality of care through practical recommendations on modifiable factors.

### **5.1 Research Questions of the Overall Project**

The following research questions have been formulated for the overall project:

- i. What is the current reality for severely injured patients regarding their return to the workforce?

- ii. Who will be able to return to work, and when?
- iii. What influencing factors (e.g., patient, occupation, accident circumstances, injury patterns, and therapy across different sectors) exist concerning the restoration of work ability, and can these be influenced?
- iv. How does health-related quality of life (hrQoL) develop over time following a severe injury until work ability is restored?
- v. What characterizes favorable and unfavorable patient pathways and trajectories?

## 5.2 Working Hypotheses of the Project

The following table (Tab. 2) presents the formulated hypotheses of the entire LeAf project:

**Tab. 2: Working Hypotheses of the Overall Project**

|              |                                                                                                                  |
|--------------|------------------------------------------------------------------------------------------------------------------|
| Hypothesis 1 | There are modifiable risk factors for the restoration of work ability in the cross-sector treatment process.     |
| Hypothesis 2 | These factors also play a relevant role in the post-traumatic condition of the patient regarding hrQoL.          |
| Hypothesis 3 | PREMs assist in identifying such factors and in developing recommendations and measures to improve patient care. |

*hrQoL = health-related quality of life; PREMs = patient-reported experience measures*

## 6. Study Population

### 6.1 Inclusion and Exclusion Criteria

The following table (Tab. 3) presents the formulated inclusion and exclusion criteria for the study population.

**Tab. 3: Inclusion and Exclusion Criteria**

| Study Part                      | Inclusion Criteria                                                                                                                                             | Exclusion Criteria                                                                                                                                                                                                                                                                                                                                                                                            |
|---------------------------------|----------------------------------------------------------------------------------------------------------------------------------------------------------------|---------------------------------------------------------------------------------------------------------------------------------------------------------------------------------------------------------------------------------------------------------------------------------------------------------------------------------------------------------------------------------------------------------------|
| Prospective Cohort Study | 
 
Severely injured patients of working age (18-55 years) with an injury severity of MAIS* <math>\geq 3</math>;
 
 | 
 
Patients who are not communicative after the acute phase (inclusion point) (Glasgow Outcome Score <math>< 3</math>)
 
Insufficient German language skills (at least B1 language level according to the European Reference Framework)
 
Patients after a suicide attempt
 
Patients without a permanent residence or residing abroad
 
 |
| DGU Trauma Register      | 
 
Admission of a patient via the emergency room with subsequent intensive therapy
 
                              | 
 
Patients with less severe injuries
 
                                                                                                                                                                                                                                                                                                                          |

| Study Part          | Inclusion Criteria                                                                                                                                                                                                                                                                                                                                                 | Exclusion Criteria                                                                                                                                                                                              |
|----------------------------|---------------------------------------------------------------------------------------------------------------------------------------------------------------------------------------------------------------------------------------------------------------------------------------------------------------------------------------------------------------------------|------------------------------------------------------------------------------------------------------------------------------------------------------------------------------------------------------------------------|
|                            | 
 
• All patients documented in the TR with a MAIS* <math>\geq 3</math>,
 
• Acute stay survived
 
• Age 18-55 years
 
• Accident date 2015-2017
 
                                                                                                                                                      | 
 
• Patients after a suicide attempt
 
• Patients who are not communicative after the acute phase (inclusion point) (Glasgow Outcome Score <math>< 8</math>)
 
 |
| WIdO Secondary Data | 
 
• Insured individuals of working age (18-55 years)
 
• Severe acute hospital-treated injury survived between 2015 and 2017 and continuously insured during the observation period. The defined severe injury must correspond to a MAIS* of at least 3 (MAIS <math>\geq 3</math>) or an ISS* <math>\geq 9</math>.
 
 |                                                                                                                                                                                                                        |

\*MAIS = Maximum Abbreviated Injury Scale; ISS = Injury Severity Score

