It is assumed that the consent rate for participation in the study will be about 50% (Kaske, 2019), of which it is expected that 25-30% will not complete the follow-up. According to experience from the DGU Trauma Register, an average of 120 severely and critically injured patients ( $\text{MAIS} \geq 3$ ) are treated annually in a Level-1 trauma center in Germany. After accounting for deceased patients (approximately 10%), around 100 patients remain per year. With a participation rate of 50% ( $n=50$ ) and an assumed maximum lost-to-follow-up rate of 30% ( $n=35$ ), approximately 30 participating trauma centers will be necessary to obtain 1000 evaluable patient cases within a one-year inclusion phase. To estimate selection bias, the study clinics will maintain a screening log of potential study patients. Additionally, a comparison of patient characteristics with the overall cohort of the DGU Trauma Register will be made using the same inclusion criteria (representativeness). The study clinics will include DGU-certified trauma centers that treat at least 40 severely and critically injured patients annually according to the inclusion criteria of the DGU Trauma Register. Currently, 45 trauma centers have already expressed interest in participating as study clinics, treating 40-250 patients annually according to the inclusion criteria of this study, see cooperation partners. Thus, it can be expected that the target numbers will be achieved, possibly even in a shorter recruitment time.

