## **Follow-Up Assessments**

Follow-up assessments will be conducted 6, 12, and 18 months after the trauma, including the PREM and PROM developed in the project (see Figure 2). The optimal follow-up assessment processes will be developed based on the results of patient interviews, literature research, and discussions with stakeholders from previously conducted follow-up studies on severely and critically injured patients, while considering data protection and technical conditions. For the follow-up, patients will be surveyed either by mail or by phone from the respective study clinics. They will not be summoned by the study clinics. In an initial work package of the overall project, a patient group-specific assessment methodology for follow-up will be developed. If postal surveys prove to be the best method of inquiry for this patient group, responses will be returned to the treating study clinic. Other partners will not have knowledge of the patients' identities.

Figure 2: Flowchart of the Prospective Cohort Study LeAf Trauma

\*FU = Follow Up, GCS = Glasgow Coma Scale, MAIS = Maximum Abbreviated Injury Scale

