### **7.1.4 TraumaRegister DGU**

The data from the TraumaRegister DGU from the years 2015 to 2017 will be used for a more in-depth representation of the cohort, for example regarding injuries and representativeness. Many clinical data of severely and critically injured patients are documented in the TraumaRegister DGU. The application includes the standard form for collecting patients in the TraumaRegister DGU, which provides an overview of the data to be collected in the TraumaRegister DGU. The data from the TraumaRegister DGU can only be analyzed through a formal request. This procedure is regulated by the application and review process according to publication guidelines (as described here: <https://www.traumaregister-dgu.de/forschung>). The data will then only be incorporated into the project in anonymized aggregated form.

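### Tab. 3 gives two contradictory Glasgow cut-offs for one exclusion, and its register row does not match the cohort row closely enough for the comparison on the same criteria that Section 6.3.1 promises

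*Protocol*

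**What the plan says.** **Exclusion for inability to communicate.** In Tab. 3 (Section 6.1) the cohort and register rows describe this exclusion in the same words and name the same score. The cohort row gives "Glasgow Outcome Score < 3"; the register row gives "Glasgow Outcome Score < 8". The legend of the cohort flowchart (Figure 2, Section 7.1.2, Follow-Up Assessments) does not list the outcome score. It lists "GCS = Glasgow Coma Scale".

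**Entry criteria.** The cohort row admits "Severely injured patients of working age (18-55 years) with an injury severity of MAIS" of at least 3. The register row has the same age range and MAIS limit, and adds "Admission of a patient via the emergency room with subsequent intensive therapy", survival of the acute stay and "Accident date 2015-2017". Both rows exclude patients after a suicide attempt. Only the cohort row excludes patients with too little German, without a fixed address or living abroad.

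**Use of the register.** On selection bias, Section 6.3.1 names a screening log and adds that a "comparison of patient characteristics with the overall cohort of the DGU Trauma Register will be made using the same inclusion criteria (representativeness"). Section 7.1.4 describes the only register extract in the Protocol: "The data from the TraumaRegister DGU from the years 2015 to 2017 will be used for a more in-depth representation of the cohort", with injuries and representativeness as examples of its purpose. Tab. 4 sizes the register arm at 29,345, labelled as the 2019 base collective.

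**The concern.** One exclusion, defined by one named score, cannot have two cut-offs and still describe the same patients. The remaining differences between the rows point the same way: the register sample is defined by criteria that the cohort does not share, yet the Protocol relies on shared criteria for its representativeness check.

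At stake is how that check can be read. Section 6.3.1 expects half of the eligible patients to consent and up to 30% of those to be lost. If participants then differ from the register sample, the reader wants to know whether participation explains it. With unequal eligibility and a different calendar period, the comparison cannot separate these causes. Register data come only through a formal, reviewed request (Section 7.1.4), so the criteria should be settled before that request is filed.

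**Working it through.** **1. The plan's own figure.** Neither cut-off has a derivation in the Protocol, so there is nothing to reproduce. The check is a comparison of texts plus a list of scale levels.

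**2. What each cut-off keeps.** The Protocol prints no scale range. The ranges below are assumptions, shown side by side.

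| Scale (assumed range) | Cut-off < 3: excluded / kept | Cut-off < 8: excluded / kept |
|---|---|---|
| Glasgow Outcome Score, 1-5 | 1-2 / 3-5 | 1-5 / none |
| Extended version, 1-8 | 1-2 / 3-8 | 1-7 / only 8 |
| Glasgow Coma Scale, 3-15 | none / 3-15 | 3-7 / 8-15 |

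No single scale gives the two cut-offs the same meaning. If the cohort row is read on the outcome score and the register row on the coma scale, each rule can be applied, but the rows then use different measures.

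**3. The two rows of Tab. 3, line by line.**

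| Criterion | Cohort | Register | Same? |
|---|---|---|---|
| Age 18-55 | yes | yes | yes |
| MAIS at least 3 | yes | yes | yes |
| Suicide attempt excluded | yes | yes | yes |
| Survived acute stay | implied (baseline taken before discharge, Section 7.1.2) | stated | in effect |
| Glasgow cut-off | < 3 | < 8 | no |
| Emergency-room admission with intensive therapy | not required | required | no |
| Accident 2015-2017 | not required | required | no |
| Language exclusion | yes | no | no |
| Residence exclusion | yes | no | no |

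Five criteria differ. Section 8 also treats the two sets as distinct, because it speaks of patients who meet both.

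**4. How much selection the check has to detect.** Section 6.3.1 starts from about 100 surviving patients per centre and year. Consent of 50% gives 100 × 0.50 = 50; a maximum loss of 30% gives 50 × 0.70 = 35. So about 35 of every 100 available patients are evaluable.

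**5. The register number in Tab. 4.** The 29,345 cases are from 2019, outside 2015-2017, so none of them meets the Tab. 3 date criterion. The number also appears not to be age-restricted. Section 4 puts severe trauma in Germany at about 30,000 people a year, with 60% aged 18-65. If that share holds for the base collective, 0.60 × 29,345 = 17,607 would remain, before narrowing to 18-55 and to survivors.

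**6. Calendar gap.** The Protocol gives no recruitment dates. Its Interim Evaluation section dates only the routine-data analysis (October 2022 to June 2023). If recruitment is assumed to fall in 2022-2023, the gap to the register window runs from 2022 − 2017 = 5 to 2023 − 2015 = 8 years.

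**The case against.** The best defence is that the Protocol uses the register in two ways. Section 2.3.3 places it in the retrospective arm, beside the WIdO data, whose inclusion years are also 2015-2017. On that reading Section 7.1.4 describes the WIdO companion extract, while Section 6.3.1, which names no years, means a separate query on the cohort's criteria. This is possible and may be what was intended. But no second extract is described, and Section 7.1.4 itself names representativeness. At the least, the text leaves open which register years serve the check.

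Other points stand in part:

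- The intensive-therapy line may be the register's own entry condition rather than a choice of this study. Then it cannot be dropped, and the cohort side has to be aligned instead.
- The coma-scale legend suggests a mislabelled scale, and an empty extract would be noticed at once. A reader might infer that the register query must return nobody. That rests on the 1-5 range, which the Protocol does not print. The contradiction between the rows needs no such assumption.
- A reader might infer that selection bias would otherwise go unchecked. It would not: the screening log is unaffected, and baseline data allow completers to be compared with those lost to follow-up.
- The 29,345 is openly labelled and feeds no calculation, so it is a planning figure that needs a clearer label, not a sizing error.
- No analysis listed in Section 7.2 uses register data, so the main results are untouched.

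**Conclusion.** The point holds as an inconsistency in an operative selection rule. The cut-offs < 3 and < 8 contradict each other for the same exclusion and the same named score, and four further criteria differ between the rows. As written, the register row does not deliver the comparison that Section 6.3.1 describes. That much rests on the Protocol's text alone.

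Three statements depend on assumptions. The loss of every register patient assumes a 1-5 scale. The 5-8 year gap assumes recruitment in 2022-2023. The confounding by calendar time assumes that the 2015-2017 extract is the one used for the check.

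It would go too far to say that a representativeness check is impossible. Once the criteria are reconciled, a matched comparison can be made, except for language and residence if the register does not record them, which the Protocol does not say. Nor does the accident window by itself prevent the use of the same clinical criteria; it adds a difference in time. Nothing in the Protocol shows which scale or cut-off was meant. Severity: should-fix, because a named bias check is weakened while the main analyses are not affected.

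**What to change.** 1. Reconcile the scale and cut-off in both rows of Tab. 3 and in the Figure 2 legend, so that one definition applies throughout. Which one is for the authors to decide.
2. For the Section 6.3.1 check, request aggregate register cases from the cohort's actual recruitment period, with the same age, MAIS, survival and suicide-attempt criteria. Keep 2015-2017 for the comparison with WIdO, and say so in Section 7.1.4.
3. If intensive therapy is a register entry condition, restrict the cohort side of this comparison to patients who meet it. If the register does not record language or residence, report these as remaining differences.
4. Restate the register number in Tab. 4 for the criteria applied, or label 29,345 as the unrestricted 2019 base collective.

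The cost is a few wording changes and one more aggregate query within a register request that is needed in any case.
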